The overall aim of the clinical trials (F_clin_, W_clin_) is to investigate short-, medium-, and long-term health effects of a 12-week interactive web-based health program (TK-HC) compared to a 12-week non-interactive web-based health program in physically inactive (F_clin_) and overweight or obese adults (W_clin_). For this purpose, the effects of each web-based health program on primary and secondary outcomes will first be examined. The hypothesis that participation in each health program is associated with improvements will be tested. Second, the difference between the interactive and non-interactive health program will be examined in terms of their effects on primary and secondary outcomes. The hypothesis will be tested that participation in the interactive health program achieves more significant improvements than participation in the non-interactive one. Finally, the impact of program use on program effectiveness will be examined. The hypothesis that higher frequency and intensity of program use leads to better primary and secondary outcomes in comparison to program use of lower frequency and intensity will be tested.

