### 2.6. Sample Size

The sample sizes of the clinical trials (F_clin_, W_clin_) were calculated with regard to the long-term effect (t0–t3) of the respective primary outcome (F_clin_: VO_2_max, W_clin_: body weight) using G*Power software (Version 3.1) (Heinrich-Heine-Universität Düsseldorf, Düsseldorf, Germany) [109]. Based on comparable studies [50,110,111], effect sizes of Cohen’s *d* = 0.45 (F_clin_) and *d* = 0.50 (W_clin_), as well as a significance level of 0.05 and a statistical power of 0.80 were assumed. For the fitness trial (F_clin_), this resulted in a required case number of *n* = 79 for both the intervention and control groups. For the weight loss trial (W_clin_), the required case number was *n* = 64 for both study groups. Allowing for an additional dropout rate of 15% in each trial, the total target sample size was found to be *n* = 186 (93 + 93) (F_clin_) and *n* = 150 (75 +75) (W_clin_). Due to limited resources, there are no plans to exceed these sample sizes. Details can be found in the study protocol of the online trials [71].

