### 4.3. Statistical Methods

For all analyses, the IBM SPSS Statistics software (Version 28.0.0.0) (IBM Corporation, Armonk, NY, USA) [113] as well as R (Version 4.0.5) [114] and RStudio (Version 1.4.1106) [115] will be used. All primary and secondary outcomes will be assessed on a metric scale level at all measurement time points. Therefore, linear mixed models (LMMs) will be used for statistical analyses of all outcomes. In the repeated measured data, the time points will be nested within cases, so the cases will be the cluster variable. The time points will enter the model as a continuous variable from baseline (0) to the end of the study (3). Random effects for intercept will be estimated. Degrees of freedom will be calculated with Satterthwaite’s method implemented in a specific R package (lmerTest). The basic model will consist of a cross-level interaction and random effects for intercept and slopes.

Level 1:

$Outcome=\beta_{0j}+\beta_{1j}*time+\beta_{nj}*X_{nj}+r_{ij}$

Level 2:

$\beta_{0j}=\gamma_{00}+\gamma_{01}*group+\gamma_{0n}*Z_{0n}+u_{0j}$

$\beta_{1j}=\gamma_{10}+\gamma_{11}*group$ $+u_{1j}$

The cross-level interaction will be between time and the dichotomous group variable (intervention vs. control group). The fixed effect $\gamma_{10}$ will represent the average change over time, while the cross-level interaction $\gamma_{11}$ will represent the difference in change between both study groups. Possible covariates or confounding variables, such as age and gender, can enter the model at the placeholder $X_{nj}$ on level 1 or $Z_{0n}\;$ on level 2.

To analyze short- and medium-term effects, the metric scale time point variable will be changed to a factor variable. Pairwise comparisons will be used with correction for multiple testing to estimate differences between each measurement time point. We will test group differences on time points t1, t2, and t3 as between-group contrast. Within each group, we will compare baseline with program completion (t0 vs. t1) and baseline with follow-up (t0 vs. t2). Additionally, we will contrast program completion with follow-up (t1 vs. t2) and change between follow-up and the end of the study (t2 vs. t3). Moreover, there is no need to account for multiple testing for the two primary outcomes as the two clinical trials (F_clin_, W_clin_) are considered as two independent trials.

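### The long-term (t0–t3) change rests on a straight-line slope over visit codes, because the named within-group contrasts omit t0 vs. t3

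*Protocol article*

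**What the plan says.** Protocol article, Section 1 (Introduction) aims at short-, medium- and long-term effects. Its first hypothesis concerns each arm separately: "The hypothesis that participation in each health program is associated with improvements will be tested".

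Section 2.6 (Sample Size) ties the long-term effect to an interval. The sample sizes "were calculated with regard to the long-term effect (t0–t3) of the respective primary outcome".

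Section 4.3 (Statistical Methods) then has four parts that bear on this point:

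- The basic mixed model takes time as a continuous variable coded 0 at baseline to 3 at the end of study. Its coefficient γ10 is described as the average change over time, and γ11 as the difference in change between the arms.
- Time becomes a factor in order to study short- and medium-term effects. A general sentence announces multiplicity-corrected pairwise comparisons among all the time points.
- Between-group contrasts are named at t1, t2 and t3.
- The within-arm contrasts are itemised: "Within each group, we will compare baseline with program completion (t0 vs. t1) and baseline with follow-up (t0 vs. t2"), then t1 vs. t2, and finally "change between follow-up and the end of the study (t2 vs. t3").

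**The concern.** The one interval that the protocol calls long-term is the one that the itemised within-arm list leaves out. The factor-time model is introduced for the short and medium term, so the wording hands the long-term change to the continuous-time model. There it is a straight line through four visit codes.

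Those codes treat a gap of 12 weeks (t0 to t1) and two gaps of 6 months (t1 to t2, t2 to t3) as equal steps. The intervention also ends at t1, so a course that moves up to t1 and then levels off or fades is plausible. On such a course the slope does not measure the difference between the last visit and baseline. The statement about each program's long-term effect, and the between-arm comparison read from γ11, could then be too small or point the wrong way.

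**Working it through.** **1. What the sample size describes.** Inputs from Section 2.6: "effect sizes of Cohen’s *d* = 0.45 (F_clin_) and *d* = 0.50 (W_clin"), and "a significance level of 0.05 and a statistical power of 0.80 were assumed". Sidedness is not stated. A two-sided, two-sample t-test with 1:1 allocation (noncentral t) gives:

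- d = 0.45: 78.49, rounded up to 79 per arm. The plan says "this resulted in a required case number of *n* = 79 for both the intervention and control groups".
- d = 0.50: 63.77, rounded up to 64 per arm. The plan says "the required case number was *n* = 64 for both study groups".

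A one-sided test gives 62 and 51 and does not match. The stated figures are therefore those of a two-sided comparison between independent groups, not of a within-arm change.

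**2. Which pairs are named.** Four time points give 4 × 3 / 2 = 6 pairs. Four are itemised within arm: t0–t1, t0–t2, t1–t2 and t2–t3. The two left out are t0–t3 and t1–t3.

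**3. What the slope estimates.** Take complete, balanced data, so that the fixed slope equals the least-squares slope through the four visit means. The codes 0, 1, 2, 3 have mean 1.5, deviations -1.5, -0.5, 0.5, 1.5 and sum of squares 5. The slope is Σ(deviation × y)/5. Multiplied by 3 steps, the implied t0–t3 change is

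-0.9·y0 - 0.3·y1 + 0.3·y2 + 0.9·y3.

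Setting this equal to y3 - y0 gives 0.3(y2 - y1) = 0.1(y3 - y0), that is, y3 - y0 = 3(y2 - y1). A straight line over the visit codes satisfies this; an early change followed by a plateau or a reversal does not.

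**4. Size under assumed courses.** The protocol gives no expected course, so these are illustrations (rows 3 and 4 read as kg):

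| Means at t0, t1, t2, t3 | Actual y3 - y0 | Slope-implied | Result |
|---|---|---|---|
| 0, 1, 2, 3 | 3 | -0.3 + 0.6 + 2.7 = 3.0 | no shortfall |
| 0, 1, 1, 1 | 1 | -0.3 + 0.3 + 0.9 = 0.90 | 10% too small |
| 0, -4, -3, -1.5 | -1.5 | 1.2 - 0.9 - 1.35 = -1.05 | 30% too small |
| 0, -4, -2, -0.5 | -0.5 | 1.2 - 0.6 - 0.45 = +0.15 | wrong sign |

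The same weights apply to γ11, with the between-arm differences in visit means in place of y.

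**5. Whether recoding time would cure it.** Taking 6 months as 26 weeks, the visits fall at weeks 0, 12, 38 and 64. The weights become -0.749, -0.434, 0.250 and 0.933, and the course 0, 1, 1, 1 gives -0.434 + 0.250 + 0.933 = 0.749, a 25% shortfall instead of 10%. The straight-line assumption causes the problem, and true visit spacing does not remove it.

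**6. Whether the named t3 contrast fills the gap.** It is a difference in level at t3. If the factor model keeps a free baseline group term, as the basic model does (γ01), the t3 difference equals the baseline difference plus the difference in t0–t3 change. It says nothing about whether either arm improved.

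**The case against.** Four points can be made in the plan's defence.

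- The general sentence on pairwise comparisons, read literally, covers all six pairs, and the four named contrasts could be highlights. This stands in part. The text is inconsistent and does not clearly exclude t0 vs. t3. But the sentence follows directly on the restriction to short- and medium-term effects, and a specific list without t0–t3 comes after it. The reading also decides how many comparisons the correction covers.
- The basic model runs from baseline to end of study and is evidently meant for the long term. Under 0/1 group coding it gives γ10 for one arm and γ10 + γ11 for the other. This stands: a model-based long-term estimate exists. The weakness is that it depends on linearity.
- The t0–t3 change is the sum of two named contrasts, t0–t2 and t2–t3. That is true of the point estimate. No test or interval is named for the sum, and two separate p-values do not supply one.
- The 30% figure comes from one chosen course. This is correct, which is why a range is shown.

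A reader might infer more: that the long-term hypothesis has no estimate at all, or that the comparison on which the trials are sized is missing. The document supports neither. The slope is an estimate, the sample size reproduces as a between-group comparison, and a between-group contrast at t3 is named. In a randomised comparison that contrast is a direct long-term result, although it is a difference in level and not in change.

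**Conclusion.** The point holds as a should-fix. Section 4.3 leaves the long-term within-arm change, and the between-arm difference in change, to a straight-line slope over visit codes, while its specific contrast list omits the t0–t3 interval and its general sentence seems to include it. The bias ranges from none to a reversed sign, depending on the course. That range assumes complete, balanced data and illustrative courses. The protocol does not say which course to expect, so no single percentage should be taken as the trial's error.

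The gap is widest for the within-program hypothesis, for which no direct long-term contrast is named. It is narrower for the between-arm question, where the t3 contrast is available. This goes beyond detail that an article may leave to an analysis plan, because the article itself fixes the time coding, the purpose of the factor model and the list of contrasts.

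**What to change.** In Section 4.3:

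- Name t0 vs. t3 within each arm as a contrast of the factor-time model, and extend that model's stated purpose to the long term.
- Include the new contrast in the multiplicity correction.
- Reconcile the itemised list with the general sentence on pairwise comparisons, so that the number of corrected comparisons is clear.
- Report the between-arm difference in t0–t3 change from the factor-time model, with its confidence interval, as the long-term estimate in place of the linear slope.

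No extra data, participants or model are needed. The cost is one more contrast in the corrected family. As an illustration, assume that the standardised within-arm change equals the planning d, that a paired t-test is run at n = 79 or 64, and that the correction is Bonferroni within an arm (the protocol does not name a method). Power is then 0.922 (fitness trial) and 0.920 (weight trial) with four contrasts, 0.910 and 0.906 with five, and 0.898 and 0.894 with all six pairs. Adding t0 vs. t3 to the four named contrasts costs about one percentage point.

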## 4. Materials and Methods: Data Collection, Management, and Analysis

### 4.1. Data Collection Methods

Data of the clinical trials (F_clin_, W_clin_) will be collected on about 336 subjects at four measurement time points (t0, t1, t2, t3) at the DoSS. The feasibility of the data collection methods has been tested in pilot trials. The data will be collected in separated and protected premises by qualified staff using reliable and validated instruments with standardized procedures. The staff will be thoroughly instructed and trained on all measurements in a standardized manner. The data collection will be done using a case report form for each study participant. The study staff will carefully complete this form during the medical examinations, and the study director will subsequently review it to ensure high data quality. All data will be digitized and subjected to final plausibility checks. The system usage data collection methods are described in the study protocol of the online trials [71].

Various measures are planned to promote participant retention and complete follow-up to make data sets as complete as possible. First, for successful trial participation, the study participants will receive free medical examinations, an activity tracker (Fitbit Charge 3^TM^), a shopping voucher, discount vouchers, and free access to the current version of the TK-HC. Moreover, the participants will be reminded of each medical examination, and all examinations will be scheduled in advance. Furthermore, participant retention and usage behavior data will be monitored. The reasons for non-retention and non-adherence will be documented for data analysis and interpretation. If subjects do not adhere to the intervention protocols, all outcome data will still be assessed. For data analysis, however, non-adherent participants will be considered by including the usage behavior data.

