According to the intention-to-treat (ITT) principle, all randomized cases will be included. In addition, only cases that have followed the per-protocol (PP) principle will be analyzed. While for ITT analysis, missing values will be imputed, in PP (complete case) analysis, only study participants with no missing values for the corresponding outcome will be analyzed. The ITT and PP analysis will be compared. An assessment of completed measurement time points will be used to test whether study participants who have completed all medical examinations differ in the corresponding outcome. Multiple imputation will be used to impute missing data in the ITT analysis. Influx and outflux statistics will be applied to identify factors that will serve as auxiliary variables for the imputation model. Sensitivity analysis will be performed to compare imputed with not imputed data.

The usage behavior data will be analyzed between the intervention and control group and within the intervention group. The analysis between the study groups will be done descriptively. For the analysis within the intervention group, the outlined model will be modified. Therefore, the group variable will be omitted, and a variable that codes usage behavior will replace the group variable in the model on level 2.

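### Influx and outflux, the only stated criterion for choosing auxiliary variables, measure completeness and not relevance, so they can screen variables for the imputation model but cannot identify useful ones

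*Protocol article*

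**What the plan says.** All of the following is in section 4.3 (Statistical Methods) of the protocol article unless noted.

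- The analysis set: "According to the intention-to-treat (ITT) principle, all randomized cases will be included".
- The missing-data method: "Multiple imputation will be used to impute missing data in the ITT analysis".
- How auxiliary variables are found: "Influx and outflux statistics will be applied to identify factors that will serve as auxiliary variables for the imputation model". The text gives no second criterion, no ranking and no cut-off.
- Two related checks: a comparison of people who attend every examination with the rest on the outcome concerned, and "Sensitivity analysis will be performed to compare imputed with not imputed data". Neither is linked to the choice of auxiliary variables.
- Section 4.1 adds: "The reasons for non-retention and non-adherence will be documented for data analysis and interpretation". This too is not tied to the imputation model.

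**The concern.** An auxiliary variable improves an imputation if it predicts the missing outcome, and it removes bias if it is also related to why the outcome is missing. Influx and outflux look at neither. They describe how a variable's gaps line up with gaps elsewhere in the data set, which tells the analyst whether the variable is present when it is needed. That is a sensible usability screen, but the article gives it the job of identifying the auxiliaries.

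The choice matters here because the primary analysis is already a linear mixed model on four time points. Imputing first adds information mainly through variables outside that model. If those are chosen for completeness, the imputed analysis may do no better than the unimputed one, although the trial holds data that could make missing-at-random more plausible.

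It matters most for people with no clinic outcome at all. Under section 2.7, people found ineligible after randomization are not examined but stay randomized, and section 4.3 includes all randomized cases. Apart from group, their imputed values rest on whatever other variables enter the imputation model.

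**Working it through.** **1. Definitions.** Let r_ij = 1 if variable j is observed for person i, and 0 if not.

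- Influx of j = Σ_k Σ_i (1 − r_ij) r_ik / Σ_k Σ_i r_ik
- Outflux of j = Σ_k Σ_i r_ij (1 − r_ik) / Σ_k Σ_i (1 − r_ik)

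Only the indicators r appear. No data value enters, so no association can.

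**2. Complete variables cannot be told apart.** Simulated data: 186 people (the F_clin target in section 2.6) and five variables, namely baseline outcome, a predictor P, a noise variable U, group, and the t3 outcome. Only the t3 outcome has gaps, in 26 people (26/186 = 14.0%).

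- Cells: 186 × 5 = 930, of which 930 − 26 = 904 are observed.
- Influx of the t3 outcome = 26 × 4 / 904 = 0.115. Influx of every other variable = 0.
- Outflux of every complete variable = 26/26 = 1.
- Sample correlation with the t3 outcome: P 0.49, U 0.05.

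P and U get identical scores.

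**3. An incomplete predictor ranks below noise.** A second draw gave P a 10% chance of being missing. P was missing in 23 people and the t3 outcome in 23, with 4 missing both.

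- Outflux of P = (23 − 4)/(23 + 23) = 19/46 = 0.41.
- Outflux of U = 46/46 = 1.00.

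**4. Which trial variables this touches** (sections 2.4.2 and 2.4.3).

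- Tracker data are collected daily from t0 to t1, and diet records in the seven days before t1, t2 and t3. Both can exist when a visit is missed, and both can have gaps that lower their score.
- Logged activities exist only in the intervention group, so they are empty by design for the control group.
- Login frequency is recorded by the system. It is probably near-complete and would score well.

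**5. What omitting a good auxiliary costs.** From section 2.6: d = 0.45, and 79/0.85 = 92.9, so 93 per arm, which matches the plan. Assumptions not in the article: baseline–t3 correlation 0.7; an auxiliary that correlates 0.5 with the t3 residual; drop-out in the interactive arm that depends on it with logistic slope 1 or 2; 1,500 replicates.

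| Missing | Slope | Bias without auxiliary (SD) | Bias with it (SD) |
|---|---|---|---|
| 15% | 1 | +0.043 | −0.004 |
| 15% | 2 | +0.073 | +0.001 |
| 25% | 1 | +0.078 | +0.002 |
| 25% | 2 | +0.116 | +0.005 |

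At the planned 15%, the bias is 0.043/0.45 = 9.6% to 0.073/0.45 = 16.2% of the assumed effect. With a correlation of 0.3 it is about +0.02 to +0.05 SD, and it approaches zero as the association weakens. The sign depends on who drops out.

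**6. With t1 and t2 outcomes in the imputation model.** In a separate run of the 15% settings, adding these outcomes (assumed correlation 0.7, both observed) cut the bias from 0.050 to 0.039 and from 0.071 to 0.055. The reductions are 0.011/0.050 = 22% and 0.016/0.071 = 23%.

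**The case against.** A reader might infer that the stated rule itself produces a bias of 0.04 to 0.12 SD. It does not. In step 5 the auxiliary is fully observed, so its outflux is 1 and an outflux screen would keep it. The figures show what it costs to leave out a good auxiliary for any reason. Noise variables that enter alongside a good predictor do little harm.

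A reader might also infer that informative variables will be excluded. The text does not say that influx and outflux are the sole criterion, and it sets no threshold. The full plan may add selection by association. Auxiliary variables are by definition additional to the analysis model, so group and the outcome at other visits would ordinarily be in the imputation model already. The mixed model also leaves room for covariates: "Possible covariates or confounding variables, such as age and gender, can enter the model". A full predictor list is properly left to the analysis plan, and its absence is not the point here.

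Some variables that might seem wrongly penalised are not. Later-visit fat mass is measured at the same examination as the outcome, and tracker data at t2 and t3 come from the week after those visits. Both tend to be absent when the outcome is absent, and a low outflux flags that correctly.

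The completer comparison and the imputed versus unimputed comparison give some protection. They do not choose auxiliaries, however, and the second reveals little if both analyses lack the same predictor.

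All of this limits the harm. What remains is that the article does state a criterion and a purpose for it, and the criterion cannot serve that purpose.

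**Conclusion.** The point holds in a limited form. Influx and outflux are the only criterion stated for finding auxiliary variables, and they carry no information on association with the outcome or with missingness. That follows from their definition and needs no assumption.

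The practical exposure is narrow: variables that are informative but incomplete (t0–t1 tracker data, pre-visit diet records, arm-specific logged activities), and randomized people who are never examined. The article does not allow the bias to be sized. As an illustration only, omitting a variable that correlates 0.5 with the t3 residual and drives drop-out in one arm costs roughly 0.04 to 0.07 SD at 15% missing. The cost is lower if t1 and t2 outcomes are in the imputation model, and near zero if associations are weak. The sample size is unaffected.

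**What to change.** Replace the sentence on influx and outflux in section 4.3 with a rule of this content:

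- The imputation model contains the analysis-model variables (group and the outcome at all visits) and program login frequency.
- Further auxiliary variables are chosen by their association with the outcome at t1 to t3 and with missingness of that outcome.
- Outflux serves only as a floor, to drop variables too incomplete to help.

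The planned completer comparison and the documented reasons for non-retention can inform the second step. Imputing separately within each arm is an option and not part of the required change.

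The cost is one sentence and a little more analysis work. No new data are needed.

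### The planned missing-data checks all stay within missing at random or a stronger assumption, so none can show bias if drop-outs did worse than comparable completers

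*Protocol article*

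**What the plan says.** Section 4.3 (Statistical Methods) of the protocol article makes six statements that bear on missing outcomes:

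- Analysis model: "linear mixed models (LMMs) will be used for statistical analyses of all outcomes".
- ITT: "Multiple imputation will be used to impute missing data in the ITT analysis".
- Imputation model: "Influx and outflux statistics will be applied to identify factors that will serve as auxiliary variables for the imputation model".
- PP: "in PP (complete case) analysis, only study participants with no missing values for the corresponding outcome will be analyzed". The article adds: "The ITT and PP analysis will be compared".
- Completers: completed time points are used to "test whether study participants who have completed all medical examinations differ in the corresponding outcome".
- Sensitivity: "Sensitivity analysis will be performed to compare imputed with not imputed data".

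Section 2.6 (Sample Size) sizes both trials on the change from t0 to t3 and sets the expected loss: "Allowing for an additional dropout rate of 15% in each trial". Section 4.2 says that no more data are gathered once a participant withdraws from the trial. No section of the article mentions an analysis in which the unobserved values are allowed to differ systematically from what the observed data predict.

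**The concern.** Under missing at random, a participant who is missing at t3 is taken to resemble those still present who have the same observed data. The threat in these trials is that this fails. Participants know their allocation, both programs are self-directed, and the visit on which the trials are sized falls 12 months after t1. Each examination takes 2–3 hours on site in W_clin and 4–5 hours in F_clin. Someone who has regained weight or stopped training since the last visit may be less likely to attend the next one, and the earlier measurements would not show it.

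A sensitivity analysis is most useful when it relaxes the assumption that carries the main result. The comparison fixed in the article does not relax it. If the imputed and unimputed results agree, a reader could take that as evidence of robustness to drop-out, although this particular risk has not been examined.

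**Working it through.** **Inputs.** From Section 2.6: d = 0.45 (F_clin) and 0.50 (W_clin), alpha 0.05, power 0.80, drop-out 15%, 93 and 75 per arm. The documents give no figure for how drop-outs fare, so the shift k is an assumption and is shown over a range of 0.25 to 1.0 SD.

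**The plan's own figures.** A two-sided two-sample t-test at 0.05 with power 0.80 gives 79 per arm for d = 0.45 and 64 for d = 0.50, as stated. Inflating for 15% drop-out gives 2 × 79 / 0.85 = 185.9 and 2 × 64 / 0.85 = 150.6, against the stated 186 and 150. The sample sizes reproduce to within rounding and are not in question.

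**What each planned check assumes.**

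| Check in Section 4.3 | What it assumes about unobserved outcomes |
|---|---|
| Multiple imputation | Missing at random, given the outcome history and the auxiliary variables |
| Unimputed data in the mixed model | Missing at random, given what is in that model |
| Unimputed data as complete cases (the PP set) | Generally stronger: completers represent everyone, given the model |
| Completers compared with others | Uses observed values only. It can question missing completely at random but cannot test missing at random |

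**Size of the bias that would stay hidden.** Let p be the share missing at t3 and k the amount, in SD, by which drop-outs do worse than completers with the same observed data. Worse means lower VO2max or higher weight. Indices I and C are the interactive and control arms.

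Bias in favour of the interactive arm = p_I × k_I − p_C × k_C

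| Setting | k = 0.25 | k = 0.5 | k = 1.0 |
|---|---|---|---|
| 15% in both arms, shift in interactive arm only | 0.15 × 0.25 = 0.0375 | 0.15 × 0.5 = 0.075 | 0.15 × 1.0 = 0.15 |
| 20% interactive, 10% control (assumed), same shift in both | 0.025 | 0.05 | 0.10 |
| 15% and the same shift in both arms | 0 | 0 | 0 |

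In the first row an estimate of 0.45 in F_clin would stand for a true effect of about 0.41, 0.375 or 0.30. An estimate of 0.50 in W_clin would stand for about 0.46, 0.425 or 0.35. A shift in the control arm only would reverse the sign.

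For the change within one arm the bias is p × k. At 15% this is 0.0375, 0.075 or 0.15 SD in each arm, even when the arms are alike. The Introduction sets improvement within each program as a hypothesis of its own, so this matters too.

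**Simulation.** 1000 runs per setting, three visits, assumed correlation 0.7, 20 imputations, no auxiliary variables. The unimputed missing-at-random estimate was obtained by regression prediction, which gives the same point estimate as a likelihood analysis of the observed data.

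| Setting | True effect | Complete cases | Unimputed | Imputed |
|---|---|---|---|---|
| F_clin, 15%/15%, no shift | 0.450 | 0.449 | 0.448 | 0.448 |
| F_clin, 15%/15%, 1 SD in interactive arm only | 0.294 | 0.446 | 0.446 | 0.446 |
| F_clin, 20%/10%, 1 SD in both | 0.351 | 0.451 | 0.450 | 0.451 |
| F_clin, 15%/15%, 0.5 SD in both | 0.447 | 0.444 | 0.444 | 0.444 |
| W_clin, 15%/15%, 1 SD in interactive arm only | 0.348 | 0.503 | 0.503 | 0.503 |
| W_clin, 20%/10%, 1 SD in both | 0.399 | 0.497 | 0.497 | 0.497 |

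Imputed and unimputed estimates differed from run to run with an SD of about 0.01, whether the bias was zero or 0.15 SD. Their agreement carries no information about this bias.

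**The case against.** The strongest reply is that this is an omission. The article does not say that the comparison tests anything beyond missing at random, and it does not exclude further sensitivity analyses. A statistical analysis plan that is not shown may contain one. That stands as a limit on the claim: nothing in Section 4.3 is false or contradictory. But the article does not leave the matter open. It names the sensitivity analysis, and the one named cannot address the main risk.

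Five stronger readings are tempting, and the documents do not support them.

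- *A reader might infer that this is the only check on missing data.* It is not. Section 4.3 also compares ITT with PP and looks at completers. Section 4.1 records reasons for non-retention and still collects outcomes from people who do not adhere. These help, but none of them tests missing at random.
- *A reader might infer that imputed and unimputed results must agree.* They need not. The imputation model may hold auxiliary variables that the outcome model lacks. In a check with one outcome, no earlier visits and about 16% drop-out in one arm driven by an auxiliary variable correlated 0.3, 0.5 or 0.7 with the outcome, the unimputed arm mean was too high by about 0.05, 0.08 or 0.11 SD, and imputation removed the bias. Earlier visits in the mixed model would shrink that gap. The planned comparison is therefore informative about the auxiliary variables. The close agreement in the simulation above partly reflects that it had none.
- *A reader might infer that the treatment comparison is biased.* Relapse can occur in both arms, and equal drop-out with an equal shift gives no between-group bias.
- *A reader might turn this into lost power.* If interactive-arm drop-outs ended at the control mean, d would be 0.45 × 0.85 = 0.38 and 0.50 × 0.85 = 0.425, with power about 0.74 at full enrolment. Those figures describe a smaller true effect. No sensitivity analysis changes that, and the relevant quantity is the bias of the estimate.
- *A reader might infer that control-based imputation is required.* Missing a visit is not the same as stopping the program. Section 2.3.1 lets users repeat the coaching until the study ends, and Section 4.2 foresees people who leave the trial but keep using the program. Imputing them from the control arm is one defensible choice among several.

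**Conclusion.** The point holds in a limited form. Multiple imputation under missing at random is a sound main ITT analysis. The stated sensitivity analysis and the two accompanying comparisons cannot reveal drop-outs who did worse than completers with the same observed data.

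At the planned 15% drop-out, the undetected between-group bias is about 0.04 to 0.15 SD for assumed shifts of 0.25 to 1.0 SD confined to the interactive arm. It is zero if drop-out and shift are the same in both arms. Within-group change is overstated by 15% of the shift in either case. The shift is unknown, so these figures are a range and not a forecast. They cannot be put into ml/min/kg or kg, because the article gives no standard deviations.

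The share of values to be imputed could exceed 15%. Section 2.7 keeps people who fail screening after randomization in the randomized set, and Section 4.3 includes all randomized cases in the ITT analysis.

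**What to change.** Keep multiple imputation under missing at random as the main ITT analysis, and keep the comparison of imputed with unimputed data as a check on the auxiliary variables. Add to Section 4.3 a delta-adjusted tipping-point analysis at t3 for VO2max in F_clin and for body weight in W_clin:

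- After imputation, move the imputed t3 values in the unfavourable direction by a shift set separately for each arm, over a grid that includes zero, equal shifts and shifts in one arm only.
- Refit the planned model and pool the results at each grid point.
- Report the between-group estimate across the grid and the shift at which the conclusion changes, so that readers can judge whether it is plausible.
- Report the within-group changes over the same grid, since equal shifts do not cancel there.

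Control-based imputation may be added as one further scenario but is optional.

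The cost is small. The analysis reuses imputations already planned, needs no new data, visits or participants, and adds one table. The downside is that the statement of robustness may turn out less favourable.
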